## Abstract

**Background:**

Cigarette smoking negatively impacts on maternal and fetal health. Smoking cessation is one of the few interventions capable of improving pregnancy outcomes. Despite the risks, the most effective antenatal model of care for smokers is still unclear, and specific recommendations for screening for fetal growth restriction are absent.

**Methods:**

This is a pragmatic randomised controlled trial of a dedicated smoking cessation clinic versus routine antenatal care as an intervention to reduce cigarette smoking behaviour. Smoking mothers randomised to the Smoking cessation Through Optimisation of clinical care in Pregnancy (STOP) clinic will have all antenatal care provided by a team comprising an obstetrician, a midwife, and a smoking cessation practitioner. This intervention includes ultrasound screening for fetal growth restriction. The control arm comprises two groups: one receiving standard care with ultrasound screening for fetal growth restriction, and one receiving standard care with ultrasound screening for growth restriction only if clinically indicated by their healthcare provider. Four hundred and fifty women will be recruited and randomised to either intervention or control arms stratifying for age, parity, and history of fetal growth restriction.

**Results:**

The primary outcome is self-reported, continuous abstinence from smoking between the quit date and end of pregnancy, validated by exhaled carbon monoxide or urinary cotinine. The quit date is targeted as being at or before 16 weeks’ gestation and no further than 28 weeks’ gestation. The secondary outcomes are a set of variables including maternal and fetal morbidity and mortality, neonatal complications and delivery outcomes, smoking and psychological outcomes, and qualitative measures.

**Conclusions:**

Despite much research into cigarette smoking in pregnancy, the optimal model of care for these women is still unknown. This study has the potential to improve the model of antenatal care provided to pregnant women who smoke and to improve outcomes for both mother and infant.

**Trial registration:**

ISRCTN11214785. Registered on 8 February 2018.

**Electronic supplementary material:**

The online version of this article (10.1186/s13063-019-3653-4) contains supplementary material, which is available to authorized users.

## Background

Smoking in pregnancy is a risk factor associated with poor maternal and fetal outcome. It remains a significant cause of morbidity and mortality for both mother and baby. Smoking is associated with low birth weight, miscarriage, placental abruption, pre-term birth, and neonatal morbidity and mortality. In addition, smoking during pregnancy is associated with long-term consequences for the child in terms of neurological development, endocrine dysfunction, and oncogenesis [1]. Babies born to smokers are more likely to suffer sudden infant death syndrome. Children of smokers have a higher incidence of childhood asthma, behavioural disorders, and poor academic performance in school [2, 3]. Children of smokers are also twice as likely to smoke themselves later in life [4].

For other risk-conferring antepartum medical conditions such as gestational diabetes mellitus (GDM), the standard of care is a dedicated antenatal clinic for treatment. This multidisciplinary team comprises an obstetrician, a diabetologist, midwife, diabetic nurse specialist, and dietician. A dedicated diabetic antenatal clinic has been shown to reduce the rate of serious perinatal complications for women with GDM [5]. Smoking is a risk-conferring antepartum condition strongly associated with complications such as fetal growth restriction. However, there is no international consensus on how to manage pregnancies complicated by smoking other than to offer smoking cessation support.

Many trials have studied smoking cessation in pregnancy, utilising methods such as psychological interventions, nicotine replacement therapy (NRT), group therapy, motivational interviewing, incentive-based therapy, feedback interventions, and exercise. These trials have been extensively summarised by Cochrane reviews [6, 7]. There are currently no international guidelines on ultrasound screening of smokers for fetal growth restriction during pregnancy, despite smokers having babies with a lower mean birth weight than non-smokers and a higher incidence of fetal growth restriction.

Behavioural interventions are more likely to succeed in an environment enhanced by supportive policies that contextualize the intervention—for example, interventions in smoke-free hospital campuses [8, 9]. We hypothesise that providing care to smokers in a dedicated smoking cessation antenatal clinic—‘the Smoking cessation Through Optimisation of clinical care in Pregnancy (STOP) clinic’—will result in a higher rate of smoking cessation compared to routine care. This higher rate of cessation will lead to increased birth weight and improved maternal and neonatal outcomes. This clinic will draw on the unique relationship enjoyed between a woman and her clinicians during pregnancy which provides for close patient contact over a period of time, creating a catalyst for change for many women. The clinic is the intervention, rather than a single specific psychological or pharmacological intervention.

## Methods

### Study design

This is an ongoing single-centre pragmatic randomised controlled trial (RCT) which commenced in February 2018. Written informed consent for each study participant is obtained prior to any data collection. The study is registered with the International Standard Randomised Controlled Trial Number clinical trial registry (ISRCTN 11214785). The Standard Protocol Items: Recommendations for Interventional Trials (SPIRIT) checklist is provided as Additional file 2.

### Pragmatic trial protocol

The STOP trial utilises a pragmatic RCT protocol. Pragmatic trials ascertain whether a difference exists in treatment as applied in clinical practice. These trials evaluate the beneficial effect of an intervention when applied by any clinician to any patient studied. The pragmatic features of the STOP RCT are as follows:
Broad patient selection criteria, allowing enrolment of a heterogeneous patient populationAn intervention delivered by clinicians in a normal clinical setting, with a protocol that allows flexibility to adapt the intervention to individual patient needs, for example, the use of NRT by some patientsThe selection of a primary outcome that reflects a ‘real-world’ concern of both patients and clinicians: smoking cessationNon-blinding of clinicians involved in delivery of the intervention, as blinding is difficult in clinical practice due to differences in appearances of treatments, e.g. attending a specialised clinic versus attending a general clinicAnalysis based on an intention-to-treat approach, which recognises that treatment crossovers occur in ‘real-world’ clinical practice.

### Population

This trial aims to recruit women who self-report smoking at least one cigarette per day and do not have any comorbidities requiring specialist antenatal care. The inclusion and exclusion criteria are detailed in Table 1.

**Table 1 Tab1:** Eligibility criteria

Inclusion criteria:	
1	≥ 18 years old
2	Singleton pregnancy
3	Smoking ≥1 cigarette daily
4	English language spoken
Exclusion criteria:	
1	Significant maternal medical disorder, e.g. cardiac, haematological, or endocrine disease requiring specialised maternal antenatal care
2	Significant maternal psychiatric disorder, e.g. delusional or psychotic disorders, severe depression requiring hospitalisation, use of ≥ 2 psychotropic drugs for treatment
3	Serious comorbid addiction issues, e.g. opiate abuse, methadone maintenance program
4	Positive serology requiring specialised antenatal care
5	Significant fetal anomaly defined as aneuploidy, life-limiting, or lethal fetal anomaly
6	Intellectual disability or lack of capacity
7	Poor or no understanding of the English language

### Recruitment

Participants are recruited from the patient population at the Coombe Women & Infants University Hospital in Dublin, Ireland. We have multiple sources of recruitment, including:
In-hospital midwife referrals at booking visitCommunity midwife booking referralsReferral from maternity wards of smoking patients admitted in early pregnancyReferral via ultrasonographers at first scan in the pregnancyReferral from consultant at first booking visit

### Informed consent

Pregnant smokers are identified at time of booking history and have routine ultrasound confirmation of an ongoing viable pregnancy. Once inclusion criteria and exclusion criteria are applied, the woman is met by a member of the research team and given verbal and written information on the study. If she agrees to take part, she signs a written consent form. Participants are free to leave the trial at any point, in which case they are transferred back to their referring clinician.

### Ethical approval

Ethical approval was granted by the Coombe Women & Infants University Hospital Research and Ethics Committee (Study No. 25-2017). All research is carried out in accordance with the Code of Ethics of the World Medical Association (Declaration of Helsinki).

### Sample size justification

Approximately 6% of women will achieve smoking cessation with individual behavioural support via a structured intervention during pregnancy [10]. Previous large-scale trials in the UK have used a figure of 9% cessation in pregnancy unaided, with a further 6% cessation arising from an intervention [11]. Longitudinal data on pregnancy in women who quit after the first antenatal visit and before late pregnancy gives a similar figure (14.6%) [10]. We aim to double the ‘routine care’ cessation rate of 9% to give an intervention cessation rate of 18%. In terms of creating a model of care for pregnant smokers, we feel it is important to have a substantial increase in cessation rates over routine care to make it a viable clinic. Assuming a 5% level of statistical significance and 80% statistical power, the sample size is 225 per study arm. In a sensitivity analysis, under the assumption of no dropouts, the trial would have higher statistical power of precisely 90% or alternatively allow detection of a lower cessation rate of 16% in those randomised to the smoking cessation clinic.

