## Analyses

### Statistical analysis

Outcomes in the smoking cessation intervention group will be compared to those for all control patients in an intention-to-treat analysis. A 5% level of significance will be used in a chi-square test for a difference in overall smoking cessation rates. Post hoc testing will consist of comparing the two control groups, i.e. controls under routine care versus controls with third trimester study scans (screening for IUGR). In a secondary analysis, IUGR rates will be compared between the smoking cessation group and the control group screened for IUGR. An analysis of covariance (ANCOVA) analysis will be used to adjust for the stratification factors (age, parity, and history of fetal growth restriction). Intervention adherence will be assessed, and the group comparisons will be reproduced in a per-protocol population. Potential patient selection bias will be assessed using the Berger-Exner test. Statistical analysis will be performed using the STATA IC15 statistical package.

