An anticipated challenge for this study is retention of participants in the clinical trial, as our previous work has shown a relatively high rate of non-attendance amongst smokers for antenatal clinic appointments [19]. Additionally, should a smoker develop certain complications (most commonly, diagnosis of gestational diabetes requiring metformin or insulin treatment), she will require transfer out to another specialist antenatal clinic, leading to drop out.

This study may lead to an improved model of care for women who smoke in pregnancy as well as recognition that this risk factor requires specialised antenatal input from healthcare professionals.

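### With 225 per arm and no dropouts, power is 80%, not 90%, and a 16% cessation rate is not detectable with 80% power

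*Protocol article*

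**What the plan says.** All the figures are in the Sample size justification section of the protocol article, unless noted.

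- Effect: the aim is to double the routine-care "cessation rate of 9% to give an intervention cessation rate of 18" per cent.
- Size: "Assuming a 5% level of statistical significance and 80% statistical power, the sample size is 225 per study arm".
- Reserve: "under the assumption of no dropouts, the trial would have higher statistical power of precisely 90" per cent, "or alternatively allow detection of a lower cessation rate of 16% in those randomised to the smoking cessation clinic".
- Total (Abstract, Methods): "Four hundred and fifty women will be recruited", which is 2 x 225.
- Test (Statistical analysis): "A 5% level of significance will be used in a chi-square test for a difference in overall smoking cessation rates", comparing the clinic arm with all controls by intention to treat.
- Dropout (Conclusions): "An anticipated challenge for this study is retention of participants in the clinical trial". The section cites earlier non-attendance among smokers and expects some transfers to other clinics to end in dropout. No dropout rate is given anywhere.

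**The concern.** The two power statements can both hold only if 225 already includes an allowance for losses, so that 80% is the power after dropout and 90% the power without it. But 225 is what the usual formula returns for 9% versus 18% at 80% power with no losses at all, and the recruited total of 450 adds nothing to it.

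If so, 80% is the best case and the reserve of ten percentage points does not exist. Readers and the Data and Safety Monitoring Committee would be relying on a safety margin that the design lacks, in a trial that itself names retention as a challenge. A null primary result could then be read as stronger evidence of no effect than it is.

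**Working it through.** **Inputs.** From Sample size justification: p1 = 0.09, p2 = 0.18 (alternative 0.16), alpha = 0.05, n = 225 per arm. From Statistical analysis: a chi-square test for a difference, taken as two-sided (z = 1.960), without continuity correction.

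**Formulas**, with pbar = (p1 + p2)/2:

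- A = sqrt[2 pbar(1 - pbar)], B = sqrt[p1(1 - p1) + p2(1 - p2)]
- n per arm = (1.960 A + z_power B)^2 / (p2 - p1)^2
- power = Phi{[(p2 - p1) sqrt(n) - 1.960 A] / B}

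**Step 1: reproduce 225.** For 9% versus 18%, pbar = 0.135, A = 0.4833, B = 0.4791. With z_power = 0.8416, n = (0.9472 + 0.4032)^2 / 0.0081 = 225.1. The plan's figure is reproduced with zero dropout.

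**Step 2: power at 225 with no dropouts.** sqrt(225) = 15, so power = Phi[(0.09 x 15 - 0.9472)/0.4791] = Phi(0.841) = 80.0%. The plan says 90%.

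**Step 3: n for 90% power.** With z_power = 1.2816, n = (0.9472 + 0.6139)^2 / 0.0081 = 300.9, so 301 per arm.

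**Step 4: the 16% claim.** For 9% versus 16%, pbar = 0.125, A = 0.4677, B = 0.4651.

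- Power at 225 = Phi[(0.07 x 15 - 0.9167)/0.4651] = Phi(0.287) = 61.3%.
- n for 80% power = (0.9167 + 0.3914)^2 / 0.0049 = 349.2, so 350 per arm.
- Solving the power formula at n = 225 for 80% power gives a smallest detectable rate of 18.0%.

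**Step 5: other methods at 225 per arm, no dropouts.**

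| Method | Power, 18% | Power, 16% |
|---|---|---|
| Two-sided, pooled | 80.0% | 61.3% |
| Two-sided, unpooled | 80.5% | 61.7% |
| Two-sided, arcsine | 80.8% | 62.0% |
| Two-sided, exact power of the chi-square test | 80.9% | 62.1% |
| Two-sided, continuity-corrected | 75.9% | 55.7% |
| One-sided 5%, pooled | 87.7% | 72.7% |
| One-sided 5%, arcsine (highest) | 88.2% | 73.3% |

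No two-sided method comes within nine points of 90%. No method gives 80% power at 16%.

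**Step 6: power under losses.** The loss rates are assumptions, as the article gives none. Both columns also assume that 9% and 18% are the rates among women who stay in the trial. Counting lost women as smoking multiplies both rates by (1 - loss) at n = 225. Excluding them keeps the rates and reduces n.

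| Loss | Counted as smoking | Excluded (n left per arm) |
|---|---|---|
| 10% | 75.0% | 75.8% (203) |
| 15% | 72.2% | 73.2% (191) |
| 20% | 69.3% | 70.7% (180) |
| 25% | 66.1% | 67.9% (169) |

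**The case against.** **The origin of 225 is not stated.** A one-sided 5% test needs 178 per arm for 80% power, and 178/0.8 = 222.5, so 223 after 20% loss. That lies close to 225 and would explain why the authors thought an allowance was included. But its no-dropout power is about 88%, not precisely 90%, and its smallest detectable rate at 80% power is 16.8%, not 16%. One-sided testing is not mentioned and does not fit a chi-square test for a difference. This route does not rescue the claims.

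**Dropout may already be inside the rates.** If 9% and 18% are rates among all randomised women, with losses counted as smoking, no inflation is needed and the 80% stands despite dropout. This is a fair point, and it makes the loss table conditional. The article does not say so, however, and its own sentence treats dropout as lowering power. Even on this reading, 225 analysed per arm gives 80%, so the 90% and 16% figures remain wrong.

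**Counting lost women as smoking is not written out.** The article says that it follows the Russell Standard but does not state this rule. The rule is therefore an assumption here. Excluding lost women gives nearly the same power.

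**How the error arose is a guess.** Removing 25% from 301 leaves 301 x 0.75 = 225.75, so a planned inflation that was never applied is possible. But the article contains no 25% dropout figure, and about 300 per arm would give only about 74% power for 16%. Nothing here depends on this explanation.

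**The effect size is a separate matter.** At the 15% implied by the earlier UK trials (9% + 6%), power is 50%. The article chose doubling deliberately, so this is context and not an error.

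**Conclusion.** The concern holds. On the plan's own inputs and a two-sided 5% chi-square test, 225 per arm with no dropouts gives 80.0% power for 9% versus 18%, ten points below the stated 90%. For 9% versus 16% power is 61%. Reaching the stated figures would take 301 per arm (301/225 = 1.34, about a third more) or 350 per arm (350/225 = 1.56, over half more).

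These results rest only on figures in the article and the two-sided reading of the test. On that reading 225 holds no margin for losses. How far power falls below 80% depends on the loss rate and on whether the 9% and 18% already count lost women as smoking; the article states neither. The recruited number and the 80% for 9% versus 18% with no loss are unaffected.

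**What to change.** Delete the sentence claiming 90% power or detection of 16%. Replace it with wording such as: *With a two-sided 5% chi-square test, 225 women per arm give 80% power for 9% versus 18% if none are lost, and 61% power for 9% versus 16%. No allowance for dropout has been added. If 9% and 18% apply to women who are followed up, and lost women are counted as smoking, power is about 75% with 10% loss and 69% with 20% loss.*

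If the sponsor did intend the two rates to apply to all randomised women with losses counted as smoking, the text should say that instead, and the loss figures can go.

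In the same edit, align the 225 per arm and 450 total with the 226 controls (113 + 113) in the Controls section. The unrounded 225.1 rounds up to 226, and the change in power is under 0.2 points.

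The cost is wording only: no extra patients and no change to the primary test, but a less favourable power statement. Should the sponsor prefer to keep 80% power after losses, dividing 226 by (1 - loss) gives 252, 266 or 283 per arm for an assumed 10%, 15% or 20% loss with lost women excluded. That would be a separate decision with a recruitment cost.

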### Randomisation

Patients are randomised on a secure data spreadsheet using a computer-generated random allocation list with allocation concealment. We are utilising block randomisation (block size of 4) with stratification for age, parity, and history of previous fetal growth restriction (see Fig. 1: trial schema).

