### Blinding

The nature of the intervention does not permit blinding of either patient or clinician, but the data entry and statistical analysis are blinded procedures. This is achieved by data entry from an electronic database using study number only, rather than identifiable patient details. Additionally, the statistical analysis is carried out on a finalised database remote from the study centre and using study numbers only.

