### Trial status

The trial protocol is version 1, 01 February 2018. Recruitment began in February 2018, and the projected recruitment end date is April 2020.

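### A single published block size of 4 in an unblinded, single-centre trial lets up to one third of allocations be predicted by a recruiter who knows the size and tracks earlier allocations

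*Protocol article*

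**What the plan says.** The Randomisation section of the protocol article gives the mechanism: "Patients are randomised on a secure data spreadsheet using a computer-generated random allocation list with allocation concealment". It then gives the block structure: "We are utilising block randomisation (block size of 4) with stratification for age, parity, and history of previous fetal growth restriction". No other block size and no variation in size is mentioned.

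Other sections set the conditions in which that list is used:

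- Study design: "This is an ongoing single-centre pragmatic randomised controlled trial (RCT) which commenced in February 2018".
- Blinding: "The nature of the intervention does not permit blinding of either patient or clinician, but the data entry and statistical analysis are blinded procedures".
- Informed consent: once eligibility is checked, "the woman is met by a member of the research team and given verbal and written information on the study".
- Trial status: "Recruitment began in February 2018, and the projected recruitment end date is April 2020".

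The Statistical analysis section plans one check on this risk: "Potential patient selection bias will be assessed using the Berger-Exner test". It also adjusts for the three stratification factors.

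**The concern.** Allocation concealment stops a recruiter from looking up the next assignment. It does not stop the recruiter from working it out. With a constant block size and visible past allocations, the last slot of every block is known, and sometimes the third slot as well. STOP and routine-care women attend different clinics in the same hospital, so staff there could learn past assignments without seeing the list.

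The primary outcome is validated continuous abstinence, which plausibly depends on a woman's willingness to quit. If a recruiter could both foresee the next slot and form an impression of motivation, more motivated women could be enrolled when a STOP slot was due. That would inflate the apparent effect of the clinic. Age, parity and previous fetal growth restriction do not measure motivation, so neither stratifying on them nor adjusting for them would remove such a bias.

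**Working it through.** **Inputs.** Block size 4 within strata (Randomisation); two arms of equal size, 225 each, so 450 in total (Sample size justification; Abstract); control arm divided 113 and 113 (Controls). The number of strata is not given, so a range is used.

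**The plan's own figure.** The article gives no predictability figure. Its sample size, which sets the scale here, reproduces. For 9% v 18%, two-sided 5%, 80% power and mean rate 0.135:

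n = [1.960·√(2·0.135·0.865) + 0.842·√(0.09·0.91 + 0.18·0.82)]² / 0.09² = (0.947 + 0.403)² / 0.0081 ≈ 225.1, which rounds up to 226 per arm against 225 stated.

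**Certain allocations, block of 4.** Write S for STOP and C for control. The six equally likely blocks are SSCC, CCSS, SCSC, SCCS, CSSC and CSCS.

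- In SSCC and CCSS, slots 3 and 4 are both determined: 2 × 2 = 4.
- In the other four, only slot 4 is determined: 4 × 1 = 4.
- Total 8 of 24 slots = 1/3 = 33.3%. Of 450 women, 450/3 = 150.

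**Best guess, always choosing the arm with more slots left.**

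- Slot 1: 1/2.
- Slot 2: 2/3.
- Slot 3: (1/3)·1 + (2/3)·(1/2) = 2/3.
- Slot 4: 1.
- Mean: (1/2 + 2/3 + 2/3 + 1)/4 = 17/24 = 70.8%, against 50% by chance.

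**If the two control groups are allocated in the same blocks (2:1:1).** Read as STOP versus control, the patterns are the same six, so the share stays at 33.3%. The exact one of three groups is certain in 7/24 = 29.2%.

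**Incomplete blocks.** Simulating 450 women spread over an assumed number of strata:

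| Strata assumed | Certain allocations |
|---|---|
| 1 | 33.2% |
| 8 | 32.6% |
| 12 | 32.3% |
| 18 | 31.7% |

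Stratification therefore hardly lowers the ceiling. What it does is make tracking more laborious.

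**Alternatives.** For the random sizes, the recruiter is assumed to know the set of sizes but not their order, with 56 women per stratum (450/8, so 8 strata assumed).

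| Scheme | Certain allocations | Best guess correct |
|---|---|---|
| Fixed 4 | 33.3% | 70.8% |
| Fixed 6 | 25.0% | 68.3% |
| Fixed 8 | 20.0% | 66.6% |
| Random 4/6 | about 5.6% | about 69% |
| Random 4/6/8 | about 2.4% | about 68% |
| Random 4/8/12 | about 2.6% | about 66% |

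**What it could do to the result (illustration only; no rates by motivation are in the documents).** Assume no true effect, 9% cessation overall and 225 per arm, and suppose that every determined slot is filled by choice. If more and less motivated women quit at 13.5% and 4.5%, the STOP rate is (2/3)·9 + (1/3)·13.5 = 10.5% and the control rate is (2/3)·9 + (1/3)·4.5 = 7.5%. That is a spurious 3 points, with about 20% false positives instead of 5%. Steering at half of those slots gives about 9%. With a 12% v 6% split the figures are about 11% and 7%.

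**The case against.** The strongest reply is that the ceiling is not the reality. Reaching one third needs knowledge of the block size and an accurate record of every earlier allocation in the same stratum, across interleaved strata formed by three factors and several referral routes. Nothing in the article says that recruiters have either. Informed consent says only that someone from the research team meets the woman. Blinding says that clinicians and patients are unblinded, not that recruiters see a running tally by stratum. Publication made the block size discoverable, but does not show that anyone used it. This stands, and the one-third figure must carry that condition.

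A reader might go further and infer that the concealment claim is false or that the list was open to recruiters. The documents do not support this. They describe a secure spreadsheet with concealed allocation. Who holds the list is a detail that an article may leave to the full protocol. The weakness is that the sequence can be inferred, not that it can be seen.

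The route through motivation is also undocumented. The article places the motivation questionnaire at the booking visit of women already in the STOP clinic. That a recruiter could sense motivation at consent is plausible, but it is an assumption.

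Finally, the investigators foresaw the risk and planned the Berger-Exner test. That deserves credit. However, the test looks for selection bias after women have been allocated, so it does not do the work of an unpredictable sequence.

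**Conclusion.** The point holds as a weakness in a stated design choice. One fixed block size of 4, in an unblinded single-centre trial whose block size became public during recruitment, allows up to 33.3% of STOP-versus-control allocations to be known in advance (about 32-33% with incomplete blocks) and about 71% to be guessed correctly. Concealing the list is therefore not enough by itself.

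These figures rest on a recruiter who knows the block size and tracks each stratum. A biased result would further need that recruiter to judge motivation and act on it. None of this is stated. The article gives no ground for saying that allocations were in fact foreseen, that selection took place, or that the 9% v 18% comparison is biased by any given amount. The case for change is that the exposure is avoidable at little cost, not that harm has been shown.

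**What to change.** For all women still to be randomised, issue a new computer-generated list with randomly varying block sizes within the same strata, and do not disclose the sizes to recruiting staff. Sizes 4, 8 and 12 are one choice: each is a multiple of 4, so they suit a 2:1:1 split if the two control groups are allocated in the same blocks, which the text does not settle. Keep the Berger-Exner test and report it separately for women randomised before and after the change.

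Under the assumptions above, certain allocations fall from about 33% to 2-3% (450 × 0.026 ≈ 12 women if applied to the whole trial, instead of 150). The best-guess rate falls only from about 71% to 66%, so predictability is reduced, not removed.

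The cost is a new list and a short amendment. Eligibility, outcomes and sample size do not change. The downside is balance: the arms can differ within a stratum by at most 4/2 = 2 women now, and by up to 12/2 = 6 in an unfinished block of 12. This matters most in small strata, such as women with previous fetal growth restriction. If that is a worry, a smaller maximum size can be chosen. Sizes 4/6/8 give a similar share of certain allocations, but a block of 6 cannot hold an exact 2:1:1 split.
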